#### Sample Size Estimation

The sample size will be calculated using G*Power software (version 3.1.9.4). Previous research has shown that a medium effect size of 0.21 is appropriate [17]. Setting a significance level of *P*<.05, a power level of 80%, and a constant correlation of 0.5, and assuming a 20% dropout rate, a total sample size of 48 participants (24 participants in each group) will be needed.

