### Data Analysis

SPSS Statistics (version 23.0; IBM Corp) will be used for the data analysis. Mean (SD) and/or median (IQR) values will be calculated for the continuous variables (eg, BMI). All of the continuous variables at T1 will be tested for between-group differences using an independent sample *t* test. Normality will be checked using Q-Q plots and tested for equal variance, as assessed by Levene’s test. If skewed, the data will be logarithmically transformed before the *t* test is applied. A repeated measures analysis of variance will be used to test for significant differences in the changes in the continuous outcome variables between the 2 groups, where group and time are the 2 factors of interest and will be controlled for significant confounding factors (eg, age). The variables will be selected in a stepwise manner, and only those with *P*<.1 will be kept in the final models. A significance level of .05 will be adopted (2-tailed test). Intention-to-treat analysis will be adopted and performed to avoid bias from withdrawals or protocol deviations.

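### The repeated measures ANOVA, as written, uses only children with all three tests, so it does not deliver the stated protection against withdrawal bias unless missing values are imputed

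*Protocol article*

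**What the plan says.** All in the protocol article:

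- **Data Analysis**, method: "A repeated measures analysis of variance will be used to test for significant differences in the changes in the continuous outcome variables", with group and time as factors and adjustment for selected covariates.
- **Data Analysis**, software: "SPSS Statistics (version 23.0; IBM Corp) will be used for the data analysis".
- **Data Analysis**, principle: "Intention-to-treat analysis will be adopted and performed to avoid bias from withdrawals or protocol deviations".
- **Sample Size Estimation**: an effect size of 0.21, with "a power level of 80%, and a constant correlation of 0.5, and assuming a 20% dropout rate", giving 48 participants, 24 per group.
- **Study Design**: outcomes are measured before the programme (T1), directly after it (T2) and 12 weeks later (T3). Follow-up testing is scheduled for everyone in both groups.
- **Data Collection Procedure**: a child absent on a test day is offered another session. This covers absence, not withdrawal.

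The article names no imputation method, mixed model or other rule for how a withdrawn child's missing T2 or T3 value enters the ANOVA.

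**The concern.** A classical repeated measures ANOVA needs a complete set of repeated measurements from each participant, and the SPSS repeated measures procedure drops the whole case if one is missing. A child tested at T1 and T2 who leaves before T3 is lost from the T2 comparison too, although the T2 value was collected.

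The Data Analysis section promises that the analysis avoids bias from withdrawals. Assigning children to their randomised group does not achieve that if those who withdraw never enter the model.

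The article gives reasons why dropout could differ between arms:

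- Only the intervention group attends 24 sessions of rising intensity, and only its sessions attract stickers and attendance rewards during the trial.
- Controls wait until after T3 for their programme, which gives them a reason to stay.
- Parents can ask for reports of their child's weight change, so a family may know of a poor response before deciding whether to continue.

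If poor responders leave one arm more than the other, the remaining complete cases are no longer a fair randomised comparison.

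**Working it through.** **1. The plan's own sample size**

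Inputs from Sample Size Estimation and Study Design: effect size 0.21, power 80%, correlation ρ = 0.5, dropout 20%, k = 2 groups, m = 3 tests; α = 0.05 from Data Analysis. Assumptions: 0.21 is Cohen's f, the test is the group-by-time interaction, and the sphericity correction is 1.

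- λ = f² × N × m / (1 − ρ); df1 = (k − 1)(m − 1); df2 = (N − k)(m − 1).
- For N = 38: λ = 0.0441 × 38 × 3 / 0.5 = 10.05, df1 = 2, df2 = 72, power 0.80. This is the smallest N that reaches 80%.
- 38 / (1 − 0.20) = 47.5, rounded up to 48. The stated figure is reproduced.
- Alternatives do not give 48 after dropout. The interaction with two tests gives 60, the between-group effect with three tests gives 153, and 38 × 1.2 gives 46.

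**2. Who would be left out**

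48 × 0.20 = 9.6, so about 10 children, leaving 38 with all three tests.

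**3. Power**

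| Loss | Complete cases of 48 | Power |
|---|---|---|
| 0% | 48 | 0.89 |
| 10% | 43 | 0.85 |
| 20% | 38 | 0.80 |
| 30% | 34 | 0.75 |

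At the planned dropout the planned power is kept. The question is bias and discarded data.

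**4. How large the bias could be (illustration only)**

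None of the dropout mechanisms below is given in the documents; all are assumptions. Set-up: three measurements with unit SD and correlation 0.5, large simulated arms, 20% lost between T2 and T3 in each arm, and no true effect. In the intervention group, the log-odds of dropout rise with a poorer T1-to-T2 change at the slope shown (per SD). In the control group loss is random, except in the last row. The figures are complete-case differences between arms in change from T1, in SD, with positive values favouring the intervention.

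| Dropout mechanism | T2 | T3 |
|---|---|---|
| Slope 0.25, intervention group only | 0.05 | 0.02 |
| Slope 0.5, intervention group only | 0.09 | 0.05 |
| Slope 1.5, intervention group only | 0.22 | 0.11 |
| Same slope and same loss in both arms | about 0 | about 0 |

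Variants at slope 1.5:

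- 10% loss per arm gives 0.12 at T2.
- 30% loss in the intervention group and 10% in the control group gives 0.32 to 0.33 at T2.
- A true effect of 0.50 is estimated as 0.72 to 0.73 at T2 and 0.61 at T3.

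A further variant linked intervention-group dropout to the T2 level rather than to the change (slope 1.2). The T3 change difference was then −0.002, in effect zero. The result depends heavily on the assumed mechanism.

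**5. What a mixed model would change**

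In every row above, dropout depends only on T1 and T2, which are observed. A correctly specified likelihood-based model keeps those values and is valid under that missing-at-random mechanism. A child who leaves during training and misses T2 has only T1. If that loss depends on the unseen T2 response, a mixed model is biased too.

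**The case against.** A reader might infer that the plan is a completers analysis that contradicts its own intention-to-treat statement. The documents do not support that. No text says that incomplete participants are deleted, and no completers set is defined. Deletion follows from the method and software, and only if nothing is imputed first. An ANOVA on imputed data for all 48 children would be compatible with intention-to-treat, and an article may leave the imputation rule to a fuller document that is not shown. The intention-to-treat sentence also covers protocol deviations, which the ANOVA does not affect.

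A reader might also take the sample size as proof, since 48 is 38 divided by 0.8. Inflating for dropout is routine under intention-to-treat as well, so it proves nothing about the analysis set.

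The larger bias figures need a steep link between response and dropout in one arm only, and the documents give no input for either feature. The simulated loss falls after T2, when training is over, so it does not represent children who quit because the programme is demanding. It is also the pattern that most favours a mixed model. Retention measures may keep loss below 20%: testing for all participants, rearranged sessions, and a coupon conditional on completing the study.

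These points stand and limit the claim. They do not remove it. The article names a specific method and claims a specific protection from it, with nothing to connect the two. If an unseen document supplies imputation or a mixed model, this section should say so; if none does, the claim is unsupported.

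**Conclusion.** The point holds in limited form. Run as written on observed data, the ANOVA would leave out up to about 10 of 48 randomised children at the planned dropout, so avoidance of withdrawal bias is not delivered unless missing values are imputed. Neither analysis as allocated nor planned power is at issue.

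The direction and size of any bias in this trial cannot be known from the documents. Under the assumptions shown, with 20% loss per arm and no true effect, the T2 estimate ranges from about 0 to about 0.22 SD, with 0.05 to 0.09 SD when the link to response is weak and in the intervention group only. The count of 10 rests on the 20% assumption and on each dropout missing at least one test. This should be fixed, but it does not invalidate the design.

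**What to change.** In Data Analysis:

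1. Replace the repeated measures ANOVA with a linear mixed model (SPSS MIXED) on all randomised participants as allocated, using every observed test, with arm-by-visit contrasts at T2 and T3. Multiple imputation before the ANOVA is an acceptable alternative if the method is named.
2. State that the analysis is valid under missing at random.
3. Add a sensitivity analysis for dropout before T2, where neither approach is protected if loss depends on the unseen response.
4. Make explicit that children who stop training are still tested at T2 and T3. Study Design already schedules follow-up testing for all participants, so this confirms that stopping training does not end testing.

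The cost is about a paragraph of text and slightly more analysis work. The named software already has the mixed-model procedure, and no extra participants or visits are needed.

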### Pilot Study

A 2-week pilot study in approximately 10 overweight/obese adolescents with mild intellectual disability will be conducted to test the data collection procedures (outcome measurements) and instruments (questionnaires) and to observe the adaptability of the intervention content. Amendments will be made where necessary. The pilot study will also be used to test the intensity of the 12 selected games. If necessary, the game order will be changed or some games may be replaced with backup games to meet the intensity requirements. The participants in the pilot study will not be involved in the main study.

## Results

This study is ongoing. The participants were recruited from October 2020 to November 2020. Total duration of the study is 13 months. Study results are expected at the end of 2021. Figure 4 shows the timeline of the study (by month).

**Figure 4 figure4:**
[figure not shown]
Study timeline.

## Discussion

Childhood obesity accompanied with lower levels of HRPF is a major threat to public health both internationally and locally [1]. Children with intellectual disability, especially adolescents, have a higher risk of being overweight/obese and having lower levels of HRPF [9,57]. Therefore, more interventions are needed to help this population attain its optimal health. However, there has been relatively limited research on this population compared with on its TD peers. The proposed PA program will address this knowledge gap by examining the success of the intervention for the target population.

This study has some limitations that need to be acknowledged. First, the PA level is a confounding variable in this study and will be collected in the form of self-reporting because most children with intellectual disability refuse to wear accelerometers, according to our previous experience. Self-reporting methods may result in problems in capturing accurate PA levels. Future studies, therefore, should consider ways to obtain PA levels from children with intellectual disability as accurately as possible. Second, results of this study cannot be applied to children with severe or profound intellectual disability because there may be possible differences associated with different levels of intellectual disability. Third, results of this study may not be applied to children studying in mainstream schools, as school settings between special schools and mainstream schools may be different.

One of the strengths of this study, in our view, is that the PA program was developed based on the results of our systematic review and meta-analysis, which was used to identify effective lifestyle interventions for reducing obesity and/or improving HRPF levels in children with intellectual disability. Other strengths of this study include the use of fun games to improve children’s motivation for participation [44]. To our knowledge, this is the first time that fun games have been adopted to tackle the target health problems in children with intellectual disability. To improve the rationality, suitability, and operability of this program, the contents of the fun games and resistance exercises will be evaluated by experts before implementation, using their vast experience in the related areas. Moreover, the RCT design with sufficient sample size, detailed inclusion and exclusion criteria, and standardized testing may improve the research quality.

If proven effective against obesity and poor HRPF, the intervention design will be made available to the participating special schools so that the intervention can continue to benefit their students. If successful, the program will also be promoted to other local special schools with students with intellectual disability. Furthermore, the study can serve as an example for international researchers, policy makers, and members of the public who are seeking to tackle the problem of obesity and poor HRPF among children with intellectual disability. The aim is to ultimately eliminate the existing health inequities between children with intellectual disability and their TD peers.

## Appendix

Multimedia Appendix 1 International BMI criteria for overweight and obesity by sex for children between 12 and 18 years old.

Multimedia Appendix 2 Details of exercise unit A.

Multimedia Appendix 3 Details of exercise unit B.

Multimedia Appendix 4 Details of exercise unit C.

Multimedia Appendix 5 Details of exercise unit D.

Multimedia Appendix 6 Details of exercise unit E.

Multimedia Appendix 7 Details of exercise unit F.

Multimedia Appendix 8 Details of 6 backup games.

## Abbreviations

CG: control group
CPF: cardiopulmonary fitness
GPAQ: Global Physical Activity Questionnaire
HR: heart rate
HRmax: maximal heart rate
HRPF: health-related physical fitness
HRR: heart rate reserve
HRrest: resting heart rate
IG: intervention group
MVPA: moderate-to-vigorous physical activity
PA: physical activity
PE: physical education
RCT: randomized controlled trial
TD: typically developing
